#### Treatment satisfaction

Treatment satisfaction is a relevant outcome measure in occupational health care and therefore another primary outcome [26]. Higher patient satisfaction is related to better patient compliance and can improve the quality of OHSs. To date, most researchers assume that patient satisfaction is best defined as a patient's evaluation of aspects of a health care service based on the fulfilment of patient expectations. Since patients, employers and health care providers (OPs) are all involved stakeholders in the RTW process, it is important to measure the treatment satisfaction of all of these stakeholders.

Patient and employer satisfaction were measured using a short version of the Patient Satisfaction with Occupational Health Professionals Questionnaire [26]. This questionnaire was designed specifically for measuring satisfaction with occupational health care. It was designed in previous research on the quality of rehabilitation of cancer survivors [27] and transferred to occupational health care in another study on employees with mental health problems [18]. The 13 items of this questionnaire refer to (a) satisfaction in general (2 items), (b) interpersonal approach (4 items), (c) communication manner (2 items), (d) professional knowledge (5 items), and (e) total satisfaction of the treatment by the OP (13 items). Respondents answered on thirteen statements on a 5-point Likert scale: 'totally disagree – disagree – no opinion – agree – totally agree' (table 2). Because a higher score indicates more treatment satisfaction, item 3,4,9,10 and 12 will be recoded. The patient satisfaction questionnaire was adapted to the situation of the employer, to measure the treatment satisfaction of the supervisor (table 3).

**Table 2 T2:** Treatment satisfaction questionnaire employee

	**Items relate to the last consultation the employee has had with the OP***
	**General satisfaction with the OP**
1	I am very satisfied about the contact with the OP
2	In general, contact with the OP made sense
	**Interpersonal approach by the OP**
3	The OP can be more respectful to me
4	The OP is more interested in the employer's, than my point of view
5	The OP seems interested in me as a person
6	The OP treats me in a pleasant manner
	**Communication manner of the OP**
7	The OP is good in explaining his or her opinion about returning to work
8	The OP listens well to what I have to say
	**Professional knowledge by the OP**
9	The OP forces me to return to work, while this is impossible
10	The OP has no experience with my kind of problems
11	The OP gives me good advice about how to deal with my health complaints
12	The OP does not seem professional to me
13	The OP knows what he/she is talking about
1–13	**Total satisfaction of the treatment by the OP **(all 13 items mentioned above)
*	5-point Likert scale from 1 (totally disagree) to 5 (totally agree)
	To increase the readability of this article we have translated the questionnaire from Dutch to English. In the study the Dutch version was used.

**Table 3 T3:** Treatment satisfaction questionnaire supervisor

	**Items relate to the last consultation your employee has had with the OP***
	**General satisfaction with the OP**
1	I am very satisfied about the contact with the OP
2	In general, contact with the OP made sense
	**Interpersonal approach by the OP**
3	The OP could be more respectful to me
4	The OP is more interested in the employee's, than the employer's point of view
5	The OP seems interested in me as supervisor
6	The OP treats me in a pleasant manner
	**Communication manner of the OP**
7	The OP is good in explaining his or her opinion about return to work of my employee
8	The OP listens well to what I have to say
	**Professional knowledge by the OP**
9	The OP forces my employee to return to work, while this is impossible
10	The OP has no experience with my kind of problems as being a supervisor
11	The OP gives me good advice about how to deal with the health complaints of my employee
12	The OP does not seem professional to me
13	The OP knows what he/she is talking about
1–13	**Total satisfaction of the treatment by the OP **(all 13 items mentioned above)
*	5-point Likert scale from 1 (totally disagree) to 5 (totally agree)
	To increase the readability of this article we have translated the questionnaire from Dutch to English. In the study the Dutch version was used.

To measure treatment satisfaction of the OPs, OPs filled in an evaluation questionnaire for each employee treated. This questionnaire consisted of 6 items, the first 4 referring to possible barriers in the RTW process and the last 2 items referring to the treatment success of their OHS (table 4).

**Table 4 T4:** Treatment satisfaction questionnaire OP

	**Process evaluation of the treatment by the OP**
1	**Which was the effect of the treatment given by the OHS on the employee,**
a)	related to recovery?*
b)	related to return to work?*
2	**Was the employee cooperative regarding the treatment?**
	a) No, not cooperative; b) Cooperative, but passive; c) Cooperative and active; d) No idea
3	**Was the employer cooperative regarding the treatment?**
	a) No, not cooperative; b) Cooperative, but passive; c) Cooperative and active; d) No idea
4	**What was the influence of the following factors on return to work of the employee?***
a)	Degree of physical work load
b)	Degree of mental work load
c)	Degree of physical work ability of the employee
d)	Degree of mental work ability of the employee
e)	Support by supervisor
f)	Support by colleagues
g)	Support by employer
h)	Work motivation of the employee
i)	Job control of the employee
j)	Relationships at work between employee and employer
k)	Duration of curative treatment
l)	Advices of the curative sector
m)	Waiting lists in the curative sector
n)	Inadequate sickness behaviour of the employee
o)	Psychosocial situation of the employee
p)	Financial situation of the employee
q)	Home situation of the employee (including care tasks)
r)	Remaining, not work-related, factors
s)	Practical (including organizational) options to work accommodations
t)	Financial circumstances employer
u)	Other factor, namely...
5	**To what extent are you satisfied by the treatment of the OHS, related to**
a)	Treatment effectiveness?**
b)	Treatment process?**
*	Response range: 1. obstructive ; 2. no effect or influence ; 3. supportive
**	7-point Likert scale from 0 (totally dissatisfied) to 6 (totally satisfied)
	To increase the readability of this article we have translated the questionnaire from Dutch to English. In the study the Dutch version was used.

### Secondary outcome

#### Cost-effectiveness measures

Cost-effectiveness of the intervention is a secondary outcome and was evaluated from the employers and the health care insurance company's perspective (expenditures for the employer and insurance company, respectively), as they are responsible for covering the costs of sick leave and treatment [28]. Direct costs of health care treatment are (table 1): (a) consultations of OPs and other OHS-professionals, (b) consultations of the psychologists from DGZ, (c) consultations of general practitioners, (d) consultations of a psychiatrist and/or psychologist and/or alternative therapist not participating in the study, and (e) medication related to the treatment of mental health problems [29].

Indirect costs are not related to health care, but are costs as a consequence of absence from work because of sickness: sick leave, disability and or death of productive persons. Costs of lost productivity caused by (partial) sick leave due to mental health problems were calculated from the net number of days of sick leave and lost earnings, as provided by the employer. Since our study took place in occupational health care and since most costs were caused by sick leave, extra efforts were made to gather reliable data on sick leave [30].

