## Methods/Design

### Study design

In a randomized controlled trial (RCT) the effect of the 'Dutch national guideline on the management of employees with mental health problems by OPs' was evaluated. The focus of this study is to examine the new, more active role of Dutch OPs according to the new guideline. Therefore, subjects in the intervention group were treated by OPs, who were trained to provide treatment according to the guideline. The control group received usual care, with minimal involvement of the OP and if applicable, access to treatment by a psychologist.

The first hypothesis of this study is that the intervention will lead to health gain for employees on sick leave due to common mental health problems. This will result in faster recovery, less stagnation and less referrals to psychologists. Counseling, instead of symptom based treatment, will result in earlier return to work and consequently a decrease of productivity loss. The second hypothesis is that the intervention will additionally lead to relatively more treatment satisfaction of the employee, the employer and the OP. The third hypothesis is that a decrease of productivity loss and prevention of expensive referrals to secondary care, will reduce costs.

The recruitment of participants for the study started in January 2002 and ended in January 2005. There was a one year follow-up. The study was funded by the Dutch Ministry of Internal Affairs and Kingdom Relations, and the Insurance Agency on Medical Guidance of the Dutch Police (DGVP). The study design, protocol and procedures were approved by the Medical Ethics Review Committee of the VU University Medical Centre.

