### Participants

#### Setting

This study was conducted with the cooperation of the Dutch police force, which is an organization with a relatively high incidence of mental health problems. These problems are mainly work related as police work has inevitable risks and stress may develop as 'part of the job' [19]. The employer of the Dutch police, the Ministry of Internal Affairs, tried to provide an optimal care and was open to alternative effective treatments. Each Dutch police employee was insured by the insurance company, the DGVP. DGVP tried to provide optimal usual care by partly financing referrals by OPs of police employees with mental health problems to a commercial psychotherapeutic centre as part of a protocol. Therefore, these police departments and their occupational health care provided a representative study population.

This intervention was developed for the occupational health care setting with its typical case load of common mental disorders. Two police departments were chosen because they had contracts with the same private OHS, i.e. Commit. Consequently, uniformity in treatment was more secured. Commit is one of the largest OHSs in the country. The police departments, i.e. Zaanstreek-Waterland and Hollands Midden, were located in the South-West of the Netherlands. Hollands Midden comprises approximately 1700 employees; Zaanstreek-Waterland approximately 800, totalling a source population of 2500 police employees.

Because we wanted to prevent employees with chronic disability to participate in the study, each employee on sick leave due to mental health problems before the start of the study in 2002, was detected by the OHS. They received a treatment by a psychologist in secondary care funded by the DGVP.

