### Interventions

#### Usual care

In this study the aim was to compare usual care of employees with mental health problems with an intervention. Usual care consisted of minimal involvement of the OP and access to treatment by a psychologist, as this represents daily practice. As the aim was to deliver the best optional care to our study population, optimal usual care was provided in this study. This consisted of the advice to OPs to refer to a psychologist, whose treatment was fully funded by the DGVP. The OP could refer to a psychologist working for a commercial multidisciplinary rehabilitation center, i.e. De Gezonde Zaak (DGZ), as this was part of an agreement with the OHS Commit. A patient was only referred if according to the expert judgement of the OP this made sense to the health condition of this person.

DGZ is one of the largest Dutch commercial psychotherapeutic intervention centers, which focuses on return to work of the employee. DGZ is located in different parts of the country. Besides physical therapists, around 100 psychologists are working for this organization. The psychologists are working according to cognitive behavioral principals. The standard therapy offered was based on protocols of the Dutch Institute for Work and Stress [20].

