OPs participating in the study received training in the guideline before the study started. During this training, consisting of a three-day course with 10–15 other OPs, knowledge about and practice in working with the guideline were educated and exchanged [21]. The course reflected the guideline by training OPs in multiple cognitive-behavioral prescriptive interventions, to stimulate the patients' acquisition of problem solving skills, and to structure the patients' daily activities. Information was given and OPs were trained to differentiate between adjustment disorder and depression, anxiety and other psychiatric disorders. Questionnaires were introduced, which can be helpful in making an accurate diagnosis. In addition, a graded activity treatment approach was introduced, which was based on a three stages model. This treatment approach resembles stress inoculation training, a highly effective form of cognitive behavioral treatment [16]. In the first stage, there is emphasis on information: understanding the origin and cause of the loss of control. Patients are also stimulated to do more non-demanding daily activities. In the second stage, patients are asked to draw up an inventory of stressors and to develop problem solving strategies for the causes of stress. In the third stage, patients put these problem solving strategies into practice and extend their activities to include more demanding ones. The patients' own responsibility and active role in the recovery process was emphasized and the same goes for the importance of an early start of the intervention aimed at the acquisition of coping skills and at regaining control. Problem solving activities according to a time contingent scheme were educated and practiced. The OPs were free to choose the specific tools for use in each phase of the process. The training course was given by four persons: an experienced OP/psychologist, a psychologist/therapist, an experienced general practitioner/researcher on emotional distress, and a psychiatrist.

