#### Co-interventions

Co-interventions cannot always be avoided. In case of post traumatic stress disorders, patients were also referred to a specialized trauma centre according to a special protocol of the DGVP. As the rehabilitation centre DGZ worked with multiple disciplines, it is possible that some patients in the control group received a combined intervention for mental and physical complaints by a psychologist and a physical therapist. In both the intervention and control groups co-interventions were registered in the medical files of the OHS and the database of the DGVP. These data can be used to adjust for co-interventions in the final multivariate analyses.

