#### Contamination

As randomization was done on patient level, OPs which were trained in the guideline treated all participants. Obviously this situation created a risk of treatment contamination between the groups. The trained OP treated an employee in the intervention group according to the guideline, as far as this happens in practice. The same OP treated an employee in the control group with minimal involvement and if applicable, direct referral to a psychologist. A cross-over learning effect may have happened in the control group, since the OP can adhere to the guideline in this group as well. The other way around, the OP may have referred an employee in the intervention group to a psychologist as well. The guideline promotes this in case of stagnation in recovery or in case of severe mental health problems of the employee. However, we tried to maximize the contrast by creating a situation in which referral to the psychologist in the control group was always granted by the insurance company (DGVP).

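### The direct-cost list omits the guideline training and, read narrowly, DGZ physical therapy; the two gaps act in opposite directions, and no payment rule is given for intervention-arm referrals

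*Protocol article*

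**What the plan says.** All references are to the Protocol article.

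- **Cost list.** Cost-effectiveness measures gives five direct-cost items: "Direct costs of health care treatment are (table 1): (a) consultations of OPs and other OHS-professionals, (b) consultations of the psychologists from DGZ", then general practitioner consultations, consultations with therapists outside the study, and medication. Table 1 has the same five, but labels the second by the participating centre and takes it from the centre's files. Costs are what the employer and the insurer spend.
- **Training.** Under Intervention: "OPs participating in the study received training in the guideline before the study started", as a three-day course. The objective and the section on guideline adherence treat this training as part of what is evaluated. Under Contamination, the same trained OPs treated both arms.
- **Physical therapy.** Co-interventions says some control patients may receive, at DGZ, "a combined intervention for mental and physical complaints by a psychologist and a physical therapist".
- **Referral funding.** Setting describes the insurer (DGVP) as "partly financing referrals by OPs of police employees with mental health problems to a commercial psychotherapeutic centre". Usual care describes "the advice to OPs to refer to a psychologist, whose treatment was fully funded by the DGVP". Contamination adds that "referral to the psychologist in the control group was always granted by the insurance company (DGVP" and gives contrast between the arms as the reason. It also says intervention patients could be referred, but no section says how those referrals were paid.
- **Hypothesis.** Study design expects that less productivity loss and "prevention of expensive referrals to secondary care, will reduce costs".

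**The concern.** A cost comparison is only as good as the match between the list of items and the care each arm receives. Here the list leaves out a resource that belongs to the guideline and, on one reading, a resource that belongs to the control arm. Because the same trained OPs saw everyone, the training does not show up as a difference between arms unless the plan assigns it to the intervention. It drops out silently.

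The funding descriptions raise a second question. If cost means what the insurer paid, and the insurer paid a different share of the same session in each arm, part of the cost difference would reflect payment rules and not resource use. The article does not say that this happened, but its wording does not exclude it either.

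At stake is the direct-cost part of the third hypothesis, above all from the insurer's perspective.

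**Working it through.** The article gives no unit prices, referral rates, number of OPs or course price, so no stated figure can be reproduced. What can be checked is the sign of each gap, with its size over assumed ranges.

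**1. Setting up the difference.** Let the saving be control minus intervention mean direct cost per patient. Let T be training cost per intervention patient and P be DGZ physical therapy cost per control patient. P in the intervention arm is taken as zero because Co-interventions names only the control group. Then

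saving on the listed items = saving on all items + T − P.

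Omitting T inflates the saving. Omitting P shrinks it.

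**2. Size of T (assumed inputs).** The planned total is 268, so 268 / 2 = 134 per arm. Assume 3 to 10 OPs at 1,000 to 3,000 euros each:

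- low: 3 × 1,000 / 134 = 22.4
- high: 10 × 3,000 / 134 = 223.9

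Spreading the cost over more patients than the trial's intervention arm would lower both figures.

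**3. Size of P (assumed inputs).** Assume 5% to 30% of control patients at 300 to 1,000 euros each:

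- low: 0.05 × 300 = 15
- high: 0.30 × 1,000 = 300

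If the Table 1 label already covers all disciplines at the centre, P is counted and this gap is zero.

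**4. Net effect, T − P.**

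- most favourable to the guideline: 223.9 − 15 = 208.9
- least favourable: 22.4 − 300 = −277.6

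The range spans zero, so the documents do not fix the direction.

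**5. Referral payment.** Take the same referral rate r and full price C in both arms, with the insurer paying all of C in control and a share s in the intervention arm. The insurer's spending then differs by rC − rsC = r(1 − s)C. If intervention referrals were also fully paid, s = 1 and the gap is zero. The documents give no s.

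**6. Source of the referral cost.** Table 1 takes DGZ consultations from the centre's files, which would allow one price per session. Data collection says direct treatment costs came from the insurer, which suggests amounts paid. The article does not say which governs.

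**The case against.** A reader might infer that the design itself manufactures the guideline's saving: referral is paid for and encouraged in the control arm only, and all the omissions favour the guideline. The documents do not support that reading, for four reasons.

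- Leaving out physical therapy lowers control cost, so it works against the saving. The Table 1 label may also cover it already, and Co-interventions says such treatment was registered in both arms.
- No section says intervention-arm referrals were only partly paid. The partial financing appears in a general description of the setting. Any percentage attached to r(1 − s)C would come entirely from an assumed s. If the employer paid the remainder, it would still be captured, because the employer's perspective is included.
- Fully funded referral is a disclosed comparator. The article calls it optimal usual care, explains its purpose, and leaves each referral to the OP's judgement. The insurer's payments are real expenditure under the stated perspective. Whether the result carries over to less generous funding is a question of generalisability.
- The third hypothesis also rests on productivity loss, and the article says most costs arise from sick leave.

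On training, it can be said that the list is for health care treatment, that the course preceded the study, and that its payer is not stated. This leaves open which perspective bears the cost. It does not justify silence, because the article makes the training part of what it evaluates.

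What stands after these objections is the missing training item, the mismatch between item (b) and Table 1, and the unreconciled funding descriptions.

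**Conclusion.** The direct-cost list is incomplete in two ways that act in opposite directions. Omitting the training understates the guideline's cost, by roughly 22 to 224 euros per intervention patient under the assumed inputs. Item (b) read narrowly understates control cost, by roughly 15 to 300 euros per control patient under the assumed inputs, and by nothing if Table 1's label governs. The actual sizes are unknown, and so is the net sign.

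The partial and full funding descriptions need reconciling, and the payment rule for intervention-arm referrals must be stated. A cost artefact from this source is possible but not shown: it requires that intervention referrals were only partly paid and that costs are taken as amounts paid.

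The point is limited to direct costs and to how the cost conclusion is worded. The productivity-loss component is untouched.

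**What to change.** In Cost-effectiveness measures, Table 1 and the costing part of Data analysis:

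1. Add the guideline training (course fee plus OP time, spread over the patients treated) to the intervention arm, at least as a stated sensitivity analysis. Say whether the employer's or the insurer's perspective bears it.
2. Widen item (b) to all DGZ sessions, including physical therapy, and use the same wording in Table 1.
3. Value each psychologist or DGZ session at one common unit price in both arms, and report payer-specific expenditure alongside so that the employer and insurer perspectives are kept. State how referrals were paid in each arm, and reconcile Setting with Usual care.
4. Report the referral component of the cost difference separately, and word the conclusion on the third hypothesis as a comparison with usual care with fully funded referral.

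Referrals, co-interventions and DGZ consultations are already recorded, so items 2 to 4 mainly need changes to wording and valuation. The training cost and number of OPs are not said to be in the collected data and would have to be obtained. The price is a little more costing work, and the result may move in either direction.
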